## Abstract

**Background:**

Parastomal hernia is a common complication of a colostomy. Ultimately, one-third of patients with a parastomal hernia will need surgical correction due to frequent leakage or life-threatening bowel obstruction or strangulation. However, treatment remains a challenge resulting in high recurrence rates. Two single center trials demonstrated that the frequency of parastomal hernias decreases by prophylactic placement of a mesh around the stoma at the time of formation. Unfortunately, both studies were small-sized, single-center studies and with these small numbers less common complications could be missed which were the reasons to initiate a prospective randomized multicenter trial to determine if a retromuscular, preperitoneal mesh at the stoma site prevents parastomal hernia and does not cause unacceptable complications.

**Methods:**

One hundred and fifty patients undergoing open procedure, elective formation of a permanent end-colostomy will be randomized into two groups. In the intervention group an end-colostomy is created with placement of a preperitioneal, retromuscular lightweight monofilament polypropylene mesh, and compared to a group with a traditional stoma without mesh. Patients will be recruited from 14 teaching hospitals in the Netherlands during a 2-year period. Primary endpoint is the incidence of parastomal hernia. Secondary endpoints are stoma complications, cost-effectiveness, and quality of life. Follow-up will be performed at 3 weeks, 3 months and at 1, 2, and 5 years. To find a difference of 20% with a power of 90%, a total number of 134 patients must be included. All results will be reported according to the CONSORT 2010 statement.

**Discussion:**

The PREVENT-trial is a multicenter randomized controlled trial powered to determine whether prophylactic placement of a polypropylene mesh decreases the incidence of a parastomal hernia versus the traditional stoma formation without a mesh.

**Trial registration:**

The PREVENT-trial is registered at: http://www.trialregister.nl/trialreg/admin/rctview.asp?TC=2018

## Background

Colorectal cancer is, together with breast cancer, the most common malignancy in the Netherlands. The incidence of colorectal cancer was over 12,000 in the year 2009. About 28,000 patients have an enterostomy, of which roughly 60% to 70% have a colostomy (Dutch Cancer Registry, Dutch Stoma Association). About half of the patients with a colostomy develop a parastomal hernia [1,2].

Probably, the true incidence is underestimated because many of these hernias are asymptomatic. Cingi *et al*. showed that 52% of their patients with a colostomy had a parastomal hernia at clinical examination, while additional computed tomography yielded an incidence of 78% [3].

Symptoms include pain due to stretching of the abdominal wall, leakage due to poor fitting appliances, skin problems, and cosmetic complaints. Moreover, bowel obstruction and strangulation of the hernia contents may be life-threatening. Despite evolution of surgical techniques, incidence rates have not declined the past 20 years [4].

Ultimately, one-third of the patients with a parastomal hernia needs surgical correction [5,6]. Parastomal hernia repair is challenging and results vary markedly between techniques. Suture repair, narrowing the opening in the fascia, is considered an obsolete procedure because the recurrence rates are over 70%. Relocation of the stoma is associated with a recurrence rate of 33% with an additional risk of developing an incisional hernia in the midline or at the old ostomy site of 20% [2,7-9]. Nowadays, prosthetic repair is the gold standard of parastomal hernia repair. Several techniques have been developed having similar results with respect to morbidity and recurrence rate (Hansson *et al.*, 2012 [10]). In the last decade, laparoscopic repair of PSH is developing. Basically two techniques are used, the modified Sugarbaker technique and the keyhole technique, of which the last seems to have a significantly higher risk of recurrence.

Because of the high incidence, inconsistent results of available data on parastomal repair and lack of sufficient treatment options, surgeons started focusing on prevention of the hernia with local reinforcement of the abdominal wall using a prosthetic mesh. At time of writing the PREVENT-trial protocol in 2009, only a few reports on this topic were published.

Two recent reviews showed that parastomal hernias can be prevented by the placement of a preperitoneal, retromuscular mesh around the stoma [11,12]. Randomized trials from Jänes and Serra-Aracil, both using a light-weight polypropylene mesh in a preperitoneal retromuscular position, found significantly more parastomal hernias in the group with a conventional stoma (53.7%) as compared to the mesh group (14.8%; *P* <0.001). Mesh related complications are rare. Serra reported one patient with a peristomal infection and one with a stenosis of the stoma. Jänes reported no mesh-related complications.

The percentage of patients with a parastomal hernia who required surgical intervention decreased in the mesh group in comparison with the non-mesh group. Both studies combined seven out of 29 patients who developed a PSH in the non-mesh group required surgical repair *versus* none of the eight in the mesh group with a PSH [13,14] (Additional file 1: Table S1).

Unfortunately the trials were small, 27 patients per group. Although a meta-analysis offers compensation for this flaw, sample size still be too small for detecting a difference when events occur infrequent. With these small numbers of patients less common complications could be missed. Furthermore the risk of bias increases due to a variability of clinical factors and non-uniform reporting of clinical parameters such as stoma site, patient characteristics, and type of surgery all contributed to the heterogeneity. To make more reliable statements on the actual decline of the incidence of PSHs, larger groups are needed.

Due to these shortcomings there is need for more methodologically sound trials.

## Methods

### Study objectives

The aim of this single-blind, multicenter, randomized controlled trial is to determine if parastomal herniation is prevented by the prophylactic placement during open surgery of a polypropylene mesh around a colostomy. Patients are blinded and are not aware if mesh placement did occur. Most surgeons will see their own patients postoperatively in the outpatient clinic so double blinding was not feasible and could not be guaranteed. Patients are randomized into two groups. In one group a preperitoneal, retromuscular positioned polypropylene mesh is placed around the stoma. In the control group a conventional stoma is created.

It is hypothesized that mesh placement will reduce the incidence of parastomal hernia of 30% down to 10%.

#### Primary endpoint

The primary endpoint is the incidence of parastomal hernia, either symptomatic or asymptomatic. In the final report, these two groups, symptomatic and asymptomatic will also be reviewed separately to see if there are more asymptomatic hernia in the mesh group.

#### Secondary endpoints

Secondary endpoints are perioperative morbidity, including stomal necrosis, stenosis, parastomal, or laparotomy wound infections. Mortality, pain, quality of life, and cost-effectiveness are other secondary endpoints that will be analyzed.

### Patient sample size

Based on available literature it is hypothesized that 30% of patients will develop a parastomal hernia, the majority in the first few years. Based on published data it is assumed that parastomal hernia will occur in 10% in the study group receiving the prophylactic mesh.

This study is powered to reveal significant differences between the two study groups. With an Alpha error of 5% (two-sided) and a Beta error of 0.10 (power of 90%), 67 patients need to be included in each arm of the trial. We decided to include a total of 150 patients which are randomly allocated in both groups. Analysis of recorded Prismant data estimate that 600 colostomies are constructed each year in the Netherlands. It is expected that the inclusion period will take 30 months and 14 hospitals are required to participate. The study started in the spring of 2010.

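### The 30% control rate is not reconciled with cited rates of about half or more, and 134 patients do not give the stated 90% power for an unqualified 20-point difference

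*Protocol article*

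**What the plan says.** The sample size section of the protocol article gives the control rate: "Based on available literature it is hypothesized that 30% of patients will develop a parastomal hernia, the majority in the first few years". For the mesh arm it says: "Based on published data it is assumed that parastomal hernia will occur in 10% in the study group receiving the prophylactic mesh". The Study objectives section repeats the same pair. The calculation follows: "With an Alpha error of 5% (two-sided) and a Beta error of 0.10 (power of 90%), 67 patients need to be included in each arm". Enrolment is then rounded up: "We decided to include a total of 150 patients which are randomly allocated in both groups".

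The abstract condenses this to one sentence without base rates: "To find a difference of 20% with a power of 90%, a total number of 134 patients must be included".

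The Background gives these rates for colostomies without mesh:

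- In general: "About half of the patients with a colostomy develop a parastomal hernia".
- In one series: 52% on clinical examination and 78% once CT was added.
- In the conventional arms of the two earlier randomised trials combined: 53.7%, against 14.8% with mesh.

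The Background also says that the true incidence is probably underestimated, because many hernias cause no symptoms. The Primary endpoint section counts symptomatic and asymptomatic hernias alike. The follow-up section defines a hernia as any detectable bulge.

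**The concern.** Two things do not fit together.

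First, 30% is attributed to the literature, but it lies at least 20 points below every no-mesh rate that the article reports. The usual explanations are not offered. A symptomatic-only rate would not match the endpoint. A stricter definition would not match the any-bulge criterion, since the 52% is itself a clinical-examination rate. A shorter horizon is not stated: the 30% has no time point, and follow-up runs to 5 years.

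Second, the power to detect a fixed absolute difference between two proportions depends on where the proportions lie. A 20-point difference is harder to detect near 50% than near 20%. A reader who takes the control rate from the Background and the power sentence from the abstract will believe that the trial has 90% power for a 20-point reduction from about half. It does not.

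What is at stake is the accuracy of the stated power and what readers take from it, particularly if the result is not significant.

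**Working it through.** **Inputs.** From the sample size section: control 30%, mesh 10%, two-sided alpha 5%, power 90%, 67 per arm (134 in total), planned enrolment 150. From the Background: about 50%, 52%, 78%, and 53.7% versus 14.8%. The last pair is 29/54 and 8/54, from two trials with 27 patients per group. Assumed here: equal allocation (75 per arm) and every patient analysed.

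**Formulas** (two-proportion test, pooled variance under the null), with D = p1 − p2, m = (p1 + p2)/2, A = √[2m(1 − m)] and B = √[p1(1 − p1) + p2(1 − p2)]:

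- n per arm = (z_alpha·A + z_power·B)² / D²
- power = Φ[(D√n − z_alpha·A) / B]

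**Step 1: the plan's own figure, 30% versus 10%.** A = √0.32 = 0.5657, B = √0.30 = 0.5477, D = 0.20.

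- Two-sided 5%: (1.960 × 0.5657 + 1.2816 × 0.5477)² / 0.04 = 1.8106² / 0.04 = 82.0, so 82 per arm (164 in total).
- One-sided 5%: (1.645 × 0.5657 + 1.2816 × 0.5477)² / 0.04 = 1.6324² / 0.04 = 66.6, so 67 per arm.

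The stated 67 is therefore the one-sided 5% result, although the text calls it two-sided. Other two-sided versions do not give 67 either: 79 with unpooled variance, 79 with the arcsine transformation, 92 with continuity correction.

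**Step 2: two-sided power at the planned pair.**

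- 67 per arm: (0.20 × 8.185 − 1.1087) / 0.5477 = 0.965, power 83%.
- 75 per arm: (0.20 × 8.660 − 1.1087) / 0.5477 = 1.138, power 87%.

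Exact enumeration gives 84% and 89% for the chi-square test, and 79% and 84% for Fisher's test.

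**Step 3: the same 20 points from a control rate of 50%.** For 50% versus 30%, A = √0.48 = 0.6928 and B = √0.46 = 0.6782.

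- 67 per arm: (1.6371 − 1.3579) / 0.6782 = 0.412, power 66%.
- 75 per arm: (1.7321 − 1.3579) / 0.6782 = 0.552, power 71%.
- For 90% power: (1.3579 + 0.8692)² / 0.04 = 124 per arm.

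**Step 4: all scenarios, two-sided 5%.**

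| Control vs mesh | Difference (points) | 67 per arm | 75 per arm | n per arm for 90% |
|---|---|---|---|---|
| 30% vs 10% (planned) | 20 | 83% | 87% | 82 |
| 50% vs 30% | 20 | 66% | 71% | 124 |
| 53.7% vs 33.7% | 20 | 65% | 70% | 128 |
| 78% vs 58% | 20 | 70% | 75% | 113 |
| 53.7% vs 14.8% (cited trials) | 38.9 | over 99% | over 99% | 30 |
| 50% vs 10% | 40 | over 99% | over 99% | 26 |
| 50% vs 16.7% (planned relative risk of 1/3) | 33.3 | 99% | 99% | 40 |

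**Step 5: are the two causes separate?** Yes. Even at one-sided 5%, 50% versus 30% has only 77% power with 67 per arm. Correcting the sidedness alone would leave the dependence on the base rate unaddressed.

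**The case against.** The strongest reply is that the low power in steps 3 and 4 needs a scenario the article never expects: a control rate near 50% with the difference still held at 20 points, hence 30–34% hernias despite mesh. The article assumes 10% with mesh and cites 14.8%. With either of those, or with the planned relative risk of one third, a control rate of 50% gives power of about 99% or more. This stands. A reader might infer that the trial is underpowered because its control rate was set too low; the documents do not support that. Against the cited difference of 38.9 points, planning for 20 is cautious.

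It can also be said that the abstract is shorthand for a pair given in full elsewhere. That explains the wording but does not rescue the number, because the 90% fails at 30% versus 10% as well. For the same reason it would be wrong to blame the control rate alone: the first cause of the shortfall is the one-sided result labelled two-sided.

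Two further inferences should be resisted:

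- *That 10% contradicts the cited 14.8%.* The latter is 8/54, with a 95% Wilson interval of about 8% to 27%, which includes 10%.
- *That no literature supports 30%.* The article is condensed and its sources are not at hand. The Background rates also come partly from colostomy patients in general, whereas this trial excludes emergency stomas, corrections and previously operated sites. The 78% adds CT, which here is done only on suspicion. What can be shown is that the article does not reconcile 30% with its own figures.

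Finally, a null result should be read from its estimate and confidence interval, not from planned power. That limits the harm but does not make the stated power correct.

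**Conclusion.** The point holds as one of reporting and justification. The article sizes the trial on a control rate at least 20 points below every no-mesh rate it cites and does not say why. Its abstract states a power that the design does not deliver at two-sided 5%: 83% (67 per arm) or 87% (75 per arm) instead of 90% at the planned pair, and 66% or 71% for a 20-point difference from a control rate of 50%. The primary comparison is not in danger if the published effect holds, since power then exceeds 99%.

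These figures rest on a pooled two-proportion test, equal allocation and no loss of patients; the article gives no dropout rate, and dropout would lower them. They do not assume that the true control rate will be 50%. They show only what follows if the cited rates apply.

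**What to change.** No extra patients and no change of design are needed.

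1. **Abstract, Methods.** Replace the unqualified 20% difference with the pair 30% versus 10% and the power actually delivered at two-sided 5%: 83% with 134 patients, 87% with 150 before dropout. Attaching 90% to that pair would still be wrong. Correct the matching power statement in the sample size section in the same edit.
2. **Patient sample size.** Label 30% and 10% as planning values, or justify them against the cited 50–54%, for example by time point or detection method. Do not put 53.7% and 14.8% in their place as the sizing basis: the trial was not sized on them, and recruitment is nearly complete.
3. **Patient sample size.** Add the power of 150 patients at the cited control rate: over 99% for 53.7% versus 14.8%, and about 70% for a 20-point difference from about 50%.

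The cost is a few sentences and a stated power that looks less favourable than 90%.

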### Trial status

The PREVENT-trial is currently open for recruitment. We expect to reach our powered number of included patients in the coming months.

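### The stated 67 patients per arm do not give 90% power at a two-sided 5% alpha; 30% versus 10% needs about 82 per arm

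*Protocol article*

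**What the plan says.** The section on patient sample size in the protocol article gives every input to the calculation. For the control arm, "it is hypothesized that 30% of patients will develop a parastomal hernia". For the mesh arm, "it is assumed that parastomal hernia will occur in 10% in the study group receiving the prophylactic mesh". The study objectives carry the same hypothesis: "mesh placement will reduce the incidence of parastomal hernia of 30% down to 10"%. The error rates and the result share one sentence: "With an Alpha error of 5% (two-sided) and a Beta error of 0.10 (power of 90%), 67 patients need to be included" in each arm. The planned total is then set at 150, allocated to both groups.

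The abstract's methods paragraph restates the result: "To find a difference of 20% with a power of 90%, a total number of 134 patients must be included". It also gives 150 as the number to be randomized. The trial status section adds: "We expect to reach our powered number of included patients in the coming months".

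The article names no test, formula, software or dropout rate for the calculation, and it nowhere mentions a one-sided test.

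**The concern.** Two event rates, an alpha with its sidedness, and a power together fix the sample size to within the choice of formula. Here the stated size is well below what the stated inputs require, so at least one of the figures is wrong.

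At stake is the type II error that readers will attach to the result. The article reports 10%. For the two-sided test it commits to, the figure at 134 patients is about 16–17%. If the trial finds no significant difference, that result would be read against a protection the design does not have. The article also justifies the trial by the small size of its two predecessors, so its own power statement should be correct.

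**Working it through.** **Inputs**, all from the protocol article: p1 = 0.30 and p2 = 0.10 (study objectives; patient sample size); alpha 5% two-sided and power 90% (patient sample size); 67 per arm, 134 in total (patient sample size; abstract); planned total 150, taken as 75 per arm because randomization is blocked by center to give similar numbers per group.

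Mean rate p̄ = (0.30 + 0.10)/2 = 0.20. Variance terms: 2 × 0.20 × 0.80 = 0.32 under the null; 0.30 × 0.70 + 0.10 × 0.90 = 0.21 + 0.09 = 0.30 under the alternative.

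**1. Reproducing the stated 67.** Pooled normal approximation, per arm:

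n = [z_α √0.32 + z_β √0.30]² / 0.20², with z_β = 1.2816.

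- Two-sided 5% (z_α = 1.960): (1.1087 + 0.7019)² / 0.04 = 81.96, so **82 per arm, 164 in total**.
- One-sided 5% (z_α = 1.645): (0.9305 + 0.7019)² / 0.04 = 66.6, so **67 per arm, 134 in total**. One-sided power at 67 is 90.1%.

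The stated figure is reproduced only with the one-sided value.

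**2. Could another standard two-sided formula give 67?** Two-sided 5%, 90% power:

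| Formula | n per arm |
|---|---|
| Unpooled variance | 78.8 → 79 |
| Arcsine | 79.0 → 79 |
| Pooled under null, unpooled under alternative (as above) | 82.0 → 82 |
| Pooled variance under both hypotheses | 84.1 → 85 |
| Log-odds | 91.5 → 92 |
| Continuity-corrected | 92 |

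The smallest of these exceeds 67 by 12 patients per arm, so neither rounding nor choice of formula explains the gap.

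**3. Two-sided power at the stated and planned sizes.** Power = Φ[(0.20 − 1.960 √(0.32/n)) / √(0.30/n)].

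- n = 67: (0.20 − 1.960 × 0.06911) / 0.06692 = 0.965; Φ = 83.3%.
- n = 75: (0.20 − 1.960 × 0.06532) / 0.06325 = 1.138; Φ = 87.2%.

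Other methods, 30% versus 10%, two-sided 5%, all patients evaluable:

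| Method | 67 per arm | 75 per arm |
|---|---|---|
| Pooled normal approximation | 83.3% | 87.2% |
| Unpooled normal approximation | 84.8% | 88.5% |
| Chi-square, exact enumeration | 84.4% | 88.5% |
| Continuity-corrected approximation | 77.1% | 82.3% |
| Fisher's exact test | 79.2% | 83.7% |

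None reaches 90% at either size.

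**4. Effect of losses.** If the 16 patients above 134 serve as a margin for losses, 16/150 = 10.7% may be lost before the evaluable number is back at 134 and pooled power at 83.3%. As an illustration only, 60 evaluable patients per arm would give about 79%. The article states no expected loss rate.

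**The case against.** The strongest reply is that the trial plans 150 patients, not 134. At 75 per arm, two-sided power is 87.2% by the pooled formula and 88.5% by exact enumeration of the chi-square test, which is 1.5 to 3 points below 90%. This stands: the fault is a misreported figure and the trial can still answer its question. It does not make the stated figures right, because both the sample-size paragraph and the abstract tie 90% power to 134 patients. Even 150 falls short of 90%, and it does so before any deaths or losses.

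A second reply is that a condensed article may leave details to a fuller document. That would cover a missing formula. Here all the inputs are printed next to a result that does not follow from them.

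Three stronger readings are tempting, and the article does not support them.

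- A reader might state as fact that the calculation was one-sided and mislabelled. The match at 66.6 is strong evidence, but the article shows no formula. Other routes come near 67 at 80% power: the two-sided log-odds formula gives 69, and 62 per arm inflated for an assumed 8% dropout gives 67 or 68. They conflict even more with the stated 90%.
- A reader might infer that recruitment could close at 134. The trial status section refers to a powered number without giving it, and the abstract and sample-size section both set the target at 150.
- A reader might combine the background's hernia rate of about half with an unchanged 20-point difference and conclude that power is far lower. The article never assumes that pairing. The earlier trials it cites, with 53.7% versus 14.8%, would give over 99% power at 67 per arm.

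**Conclusion.** The point holds as an arithmetic error in the sample-size statement. With 30% versus 10% and a two-sided 5% alpha, 90% power needs about 82 per arm (79 unpooled, 92 continuity-corrected), not 67. Two-sided power is about 83–84% at 67 per arm and about 87–89% at 75 per arm with an uncorrected test; Fisher's exact test gives 79% and 84%. The 75-per-arm figures assume an equal split and that all 150 patients are evaluable.

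The conclusion does not depend on how 67 was obtained. A one-sided calculation is the likely origin but is undocumented. The finding concerns the reported power and gives no ground to doubt the 30% versus 10% hypothesis or the recruitment target of 150.

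**What to change.** Keep the two-sided test and the planned 150 patients. In the abstract and in the patient sample size section, replace the 90% claim with wording such as: for 30% versus 10%, two-sided alpha 5% and an uncorrected test of two proportions, with all patients evaluable, 67 per arm gives about 83% power and the planned 75 per arm about 87%; 90% would need about 82 per arm. The condition on evaluable patients must stay in the sentence, because deaths or losses lower the power. If the primary test is Fisher's exact or a continuity-corrected test, quote the lower figures: 79% and 84% for Fisher, 77% and 82% for the continuity-corrected test.

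The cost is a change of wording and a less favourable stated power. No extra patients and no design change are needed.
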